# Effectiveness of theta and gamma electroacupuncture for post-stroke patients on working memory and electrophysiology: study protocol for a double-center, randomized, patient- and assessor-blinded, sham-controlled, parallel, clinical trial

**DOI:** 10.1186/s13063-020-04807-z

**Published:** 2020-11-04

**Keywords:** Post-stroke, Working memory (WM), Electroacupuncture (EA), Randomized controlled trial

## Abstract

**Background:**

Practitioners of complementary and alternative medicine have suggested that electroacupuncture (EA) could improve post-stroke cognitive impairment, based on the clinical evidence. This study protocol is aimed at showing the effectiveness of theta and gamma EA for post-stroke patients on working memory (WM) and electrophysiology.

**Methods:**

After assessing their eligibility, 66 patients with stroke will be enrolled from two Chinese medicine hospitals and randomly divided into theta frequency EA group, gamma frequency EA group, and sham-EA group according to the ratio of 1:1:1. All patients will receive 20 sessions of EA procedures for 4 weeks. Patients in three groups will receive EA at two same acupoints in the head: Baihui (GV20) and Shenting (GV24). The frequency of the three groups of EA is set as follows: 6 Hz (theta-EA group), 40 Hz (gamma-EA group), and no current through the electrodes (sham EA). Patients and assessors will be blinded throughout the entire study. The primary outcome is the performance accuracy of 1-back task which is a frequently used measure of WM in cognitive neuroscience research contexts. Secondary outcome measures will include the response time of 1-back task, the Rivermead Behavioral Memory Test, Trail Making Test, Loewenstein Occupational Therapy Cognitive Assessment Scale, modified Barthel Index, and electroencephalogram (EEG) signals during 1-back tasks. A blinding index will be assessed. Data will be statistically analyzed by one-way ANOVA, at 5% of significance level.

**Discussion:**

We expect this double-center, randomized, patient- and assessor-blinded, sham-controlled, parallel, clinical trial to explore the effectiveness of theta and gamma EA therapy, compared with sham EA, for post-stroke WM.

**Trial registration:**

Chinese Clinical Trial Registry, ChiCTR2000031995. Registered on 17 April 2020.

## Background

Cognitive dysfunction is one of the common dysfunctions in patients after stroke. The decline in cognitive function has a serious impact on patients’ quality of life and is a major factor to prevent patients from returning to society [1, 2]. Working memory (WM), an important part of cognitive function, is considered to be the basis for the brain to successfully perform complex behaviors [3]. Studies have shown that the incidence of WM disorders among post-stroke patients is as high as 87.6% [4].

As the main responsibility for information retention and processing in the brain for a short time [5], WM decline will cause a decline in overall cognitive function [3, 6]. For example, patients with WM impairment may have difficulty performing daily activities such as memorization, reading, writing, planning, coherent performances, and communication [7, 8]. For post-stroke patients, WM disorder can also reduce the efficiency of individual rehabilitation training, such as learning and maintaining new movements [9]. In addition, emotional disequilibrium and self-regulation (such as depression) may also occur due to WM deficits [8, 10]. Despite they have a high incidence in stroke patients, WM disorders are often overlooked because they are hidden [4]. Therefore, there are still few clinical studies on WM rehabilitation after stroke [11].

Acupuncture, as the main treatment method of traditional Chinese medicine, is commonly used in the clinical treatment of neurological diseases [12–14]. The method of executing electrical stimulation on the needle body after inserting the needle into the acupoints is called electroacupuncture (EA) [15]. A meta-analysis has shown that acupuncture (including EA) has a positive effect on post-stroke cognitive function [16]. Nevertheless, can EA improve WM impairment after stroke? What is the optimal frequency of EA to improve WM? It is true that we need more related clinical researches on those questions.

Current neuroscience research has found that neural oscillations play an important role in a range of cognitive function [17–21]. For example, electroencephalogram (EEG) recording shows that subjects’ oscillations in theta (3–8 Hz) and gamma (> 30 Hz) band have a special correlation with WM [22–25]. Among them, the oscillations in the theta band are responsible for organizing and arranging WM items in sequence [26]; the oscillations in the gamma band play a role in maintaining WM information [27]. In addition, many experiments have confirmed that transcranial alternating current stimulation (tACS) at theta and gamma frequencies can enhance WM in healthy subjects [18–20].

Compared with tACS, EA is a more mature and widely used clinical treatment therapy. A large number of studies have confirmed the safety and effectiveness of EA in the treatment of post-stroke patients. Collectively, this study will explore the effects of EA in the theta (6 Hz) and gamma (40 Hz) bands on WM of stroke patients and investigate changes of electrical activity in the cerebral cortex before and after intervention.

## Methods/design

### Primary objective and study hypothesis

The main purpose of this clinical trial is to observe the efficacy of EA at theta, gamma, and sham frequencies on WM. We adopt the classic evaluation paradigm of WM: using 1-back paradigm to evaluate the performance of all patients before and after intervention. Three groups of patients were compared between baseline and after intervention. It is hypothesized that EA intervention at theta and/or gamma frequencies may significantly improve patients’ WM.

### Secondary objectives

(1) Since the central executive system is an important part of WM, the study will observe changes in executive functions. (2) WM is closely related to the patient’s overall cognitive level and ability to daily life. The study will also observe patients’ behavioral memory, overall cognition level, and daily life ability. (3) By using EEG, we recorded the electrical signals of the cerebral cortex of patients during 1-back tasks. Through the analysis of the EEG data, the effects of theta-EA and gamma-EA on the electrophysiological properties of the brain will be investigated and compared with sham EA.

### Study design

This study is a two-center, randomized, sham-controlled, blinded patient and evaluator, parallel clinical trial. Our study will show if it is feasible to arrange patients randomly in EA trials of WM after stroke. The results of the study will be used to sample size calculation to provide a basis for subsequent research.

Sixty-six post-stroke patients will be recruited to participate in the trial. Before the experiment begins, the doctor will provide specific information about the trial to patients both orally and in writing. All patients will voluntarily sign an informed consent provided by the attending doctor. The informed consent was approved by the ethics committee before the formal experiment begins. All patients will be screened according to eligibility criteria. Sixty-six post-stroke patients will be randomly divided into theta-EA group, gamma-EA group, and sham-EA group according to the ratio of 1:1:1. The EA treatment and evaluation did not perform simultaneously. The evaluation will be performed the day before the intervention. The second evaluation is at least 2 h after the last intervention. All patients will receive an intervention that lasts for 4 weeks (30 min a day, 5 days a week, Monday to Friday).

Considering that the focus of this experiment is to explore the effects of EA at different frequencies on WM, patients in three groups will receive EA at two same acupoints in the head: Baihui (GV20) and Shenting (GV24). The frequency of the three groups of EA is selected as follows: 6 Hz (theta-EA), 40 Hz (gamma-EA), and no current through the electrodes (sham EA). The overall schematic diagram and schedule for the study are respectively shown in Figs. 1 and 2.

**Fig. 1 Fig1:**
[figure not shown]
Flow diagram of the study design including the process of recruitment, allocation and intervention, and assessment. EA, electroacupuncture; RBMT, The Rivermead Behavioral Memory Test; TMT, Trail Making Test; LOTCA, Loewenstein Occupational Therapy Cognitive Assessment Scale; MBI, Modified Barthel Index; new BI, new blind index

**Fig. 2 Fig2:**
[figure not shown]
Standard Protocol Items: Reccommendations for Interventional Trials (SPIRIT) figure. EA, electroacupuncture; MMSE, Mini-Mental State Examination; RBMT, The Rivermead Behavioral Memory Test; TMT, Trail Making Test; LOTCA, Loewenstein Occupational Therapy Cognitive Assessment Scale; MBI, Modified Barthel Index; new, BI new blind index

### Setting and recruitment

Eligible patients will be recruited by Yueyang Hospital of Integrated Traditional Chinese and Western Medicine affiliated to Shanghai University of Traditional Chinese Medicine and Anhui Wannan Rehabilitation Hospital. Both hospitals will post research advertisements online (website) and offline (poster) to recruit patients. To enhance recruitment quality, investigators will monitor medical records. The attending doctor will carefully inquire and record the patients’ past and present medical history.

### Ethical review and general statements

The study will be conducted in accordance with the research protocol and the current version of the Helsinki Declaration. All patients will be fully informed about the trial and sign a written informed consent form before participating. This trial was approved by the Ethics Committee of Yueyang Integrated Hospital of Traditional Chinese and Western Medicine, Shanghai University of Traditional Chinese Medicine (approval number: 2019-121), and registered in China Clinical Trial Registration Center (ChiCTR. gov) in March 2020 (registration number: ChiCTR2000031995).

### Eligibility criteria

#### Inclusion criteria

Eligible patients must meet all of the following criteria before being randomized: (a) male or female between the ages of 18 and 80; (b) diagnosis of cerebral hemorrhage or cerebral infarction by using computed tomography (CT) or magnetic resonance imaging (MRI); (c) got at least 24 points in MMSE test to ensure that the patient has not caught dementia; (d) had a stroke more than 1 month before; (e) GDS self-rating depression scale ≤ 6 points; (f) can tolerate an evaluation that lasts 2 h; (g) is consciousness and has a stable physical condition; and (h) giving verbal and written consent that signed and confirmed by the patient.

#### Exclusion criteria

Patients will be excluded if they meet one or more following criteria: (a) has severe visual and hearing problems; (b) has severe impairment in language understanding which shown by tests for aphasia screening scales; (c) has local skin infections, ulcers, and scars or is allergic to acupuncture; (d) has severe bleeding and coagulopathy; (e) body or head metal implants (except oral cavity): implantation of pacemakers, defibrillators, cochlear implants, and drug pumps; (f) skull fractures and/or severe head injury; (g) get seizures; (h) has mental disorders; (i) severe physical conditions (such as heart disease); and (j) other diseases or medical conditions that affect cognitive function.

### Randomization and allocation

For randomization, to reduce the chance of bias and confusion and increase the probability of meeting statistical analysis assumptions, a restricted randomization with a random block size between 3 and 6 will be used (the exact size is determined by an external agency) [28]. Two centers will both receive a computer-generated random list from third-party partners (MATLAB 2012b, Mathworks Inc., Natick, MA, USA) which will not participate in this research. Envelopes with sequential numbers are opaque and sealed and will be distributed to each test center by a third-party agency that is not part of the research team. Before the first treatment and after the treatment is completed, the therapist will be notified to perform a baseline and post-treatment evaluation of the patient.

### Blinding

To minimize deviations and disturbances caused by other factors, the acupuncturist will not give the patient any information about the treatment. In this study, the interventions that patients received in three groups will keep as consistent as possible except for different frequencies. Even needles’ position, angle, depth, and acupuncture technique that patients received will be kept completely consistent. Visually, the sham-EA group looks the same as the two observation groups. The electrodes will be connected to the needle body, and the EA instrument will also be turned on and modulated with the parameters. During the three groups of treatments, the EA instrument was placed on the back of the patient to ensure that the patient could not see the parameters of the stimulation. The specific stimulation scheme of sham EA will be introduced in the chapter of fake EA. The above scheme ensures that patients do not know what kind of intervention they are receiving. At the same time, assessors are not involved in the treatment to ensure the completion of the blind method. At the end of the study, patients and assessors will be asked to try to infer which group they think they belong to. Judgment results are calculated through new blindness index (BI) [29] to assess the success or failure of blinding. Unblinding should be determined on a case-by-case basis and considered only in a critical medical emergency. If unblinding happen, the subject will be terminated from the trial immediately, and the investigator will record the reason for the termination in the CRF. All data will be retrieved with the CRF after the trial, so as to analyze the reason, scope, and time of unblinding to evaluate the efficacy and safety of the study.

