#### Dropout criteria

Patients will be discontinuing interventions if they meet one or more following criteria: (a) mistakes/acceptances (subjects who were mistakenly included); (b) subjects have poor compliance and have not been treated as prescribed, for example, subjects who cannot cooperate with researchers or subjects who are unable to remain quiet and stay still or subjects who cannot come to treatment on time; (c) incomplete medical record data that affects the evaluation of efficacy; (d) subjects withdraw on their own; (e) subjects have adverse events (including recurrence of stroke or cerebral hemorrhage, stuck needles, bent needles, hematoma, pain, and metal allergy); (f) the subject’s disease has worsened severely, or some comorbidities, complications, and special physiological changes have occurred (which is unknown adverse events that we may encounter during the study); and (g) the researcher believes that the subject is not suitable to continue participating in this study.

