### Data collection methods and management

Data will be collected on Case Report Forms (CRF), which will resemble the paper forms approved by the ethics committee. The data from primary outcome and secondary outcome will be transferred from the output files and assessment forms to the CRF. An identification code will be allocated for each patient during the enrolment phase to preserve anonymity. Only CRF will be allowed to record patient identification. Two data managers will type the CRF into the computer and check the paper and the electronic data. Except for the ethics committees during audit, all data will be confidential and made anonymous to anyone outside the study. About EEG data, we will solicit participants to consent that the data will be kept at the hospital for future studies. All the data will be available from the corresponding author for use and/or analysis. During the study, If the participants discontinue or deviate from intervention protocols, we will collect as much data as possible for further analysis. Plans that promote participant retention and complete follow-up are as follows: primarily, we will strengthen the communication between researchers and patients, in order to gain the understanding and cooperation of patients as much as possible; furthermore, we will give the patients corresponding financial compensation according to the number of times the patients participated, so as to encourage the patients to continue participating in the experiment until the end of the experiment; last but not least, patients will receive free relevant examination results including cognitive assessment, etc. The results of the experiment will be used to write an article for clinical research, and the article will be published in a relevant journal for professional medical workers and the public to review. The patients will also be informed with the phone number of the attending doctor while undergoing the experiment. It is convenient for them to get more information about the experiment from the attending physician.

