#### The efficacy analysis will use an intention-to-treat analysis

The results of 1-back evaluation are based on the accuracy and response time as the observation indicators. The evaluation results of RBMT, TMT, LOTCA, and MBI are summarized according to the calculation rules of each scale. The results of each of the above assessments are expressed as mean ± SD. The statistical method uses analysis of variance (assuming a normal distribution) and using Kruskal-Wallis (non-parametric test) to test if it does not meet the normal distribution. The significance level was 95% (*p* values alpha < 0.05 on both sides). If the data is missed, the last observation carried forward method will be applied.

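### Ending trial participation on unblinding conflicts with continued data collection and the intention-to-treat analysis; the dropout list leaves the same question unclear

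*Protocol article*

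**What the plan says.** Four sections of the protocol article bear on what happens to a patient whose course departs from plan.

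- **Blinding.** Unblinding is restricted: "Unblinding should be determined on a case-by-case basis and considered only in a critical medical emergency". The consequence is then fixed: "If unblinding happen, the subject will be terminated from the trial immediately". The reason is recorded, and "All data will be retrieved with the CRF after the trial", so that the unblinding can be examined when efficacy and safety are evaluated.
- **Dropout criteria.** The operative sentence is "Patients will be discontinuing interventions if they meet one or more following criteria". The list that follows mixes clinical reasons (adverse events, worsening disease) with mistaken inclusion (a), poor compliance (b) and, as item (c), "incomplete medical record data that affects the evaluation of efficacy".
- **Data collection methods and management.** "If the participants discontinue or deviate from intervention protocols, we will collect as much data as possible for further analysis".
- **Statistical analysis.** The heading states "The efficacy analysis will use an intention-to-treat analysis", and missing data are handled by last observation carried forward.

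Study design provides two assessments: one the day before the intervention starts and one at least 2 hours after the last session. Randomization and allocation likewise places the second one after treatment is completed.

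**The concern.** Stopping the needling, leaving follow-up and leaving the analysis are three different events, and the protocol does not keep them apart. The Blinding section ends participation in the trial itself. That is hard to square with a promise to go on collecting data, or with an analysis meant to include every randomised patient with an outcome measured where possible.

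The loss would occur after randomisation and would follow serious clinical events, because unblinding is reserved for emergencies. It could also depend on arm: the Sham-EA group section gives current through the electrode as the only difference between sham and verum treatment, and Patient safety lists discomfort and needle pain as attributable to EA. If such patients miss the endpoint assessment, the comparison rests partly on carried-forward baseline values, and intention to treat is kept in name only. Sites also cannot tell from the text whether a patient who meets a dropout criterion should come back for the 1-back task.

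**Working it through.** **1. The sections side by side.**

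| Event | Section | Stops intervention? | Leaves follow-up? | Leaves analysis? |
|---|---|---|---|---|
| Unblinding | Blinding | Yes, by implication | Yes, terminated from the trial | Not stated; recorded data retrieved |
| Items (a) to (g) | Dropout criteria | Yes, in the operative words | Suggested by the heading only | Not stated |
| Discontinuing or deviating | Data collection | Already happened | No, data still sought | Data are for further analysis |
| Any randomised patient | Statistical analysis | – | – | No, intention to treat with values carried forward |

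The first row conflicts with the third on follow-up and fits badly with the fourth. The second row can be reconciled with the third and fourth if its operative words govern, but its heading points the other way.

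**2. What termination does to the primary outcome.** There is one baseline and one post-baseline 1-back. For a patient terminated between them, the last observation is the baseline score. Retrieving the CRF recovers what was recorded; it cannot supply a score that was never measured.

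**3. Item (c).** Incomplete records are a property of the data, not of the patient's condition or tolerance of treatment, so they give no reason to stop an intervention. Because the item turns on whether the efficacy evaluation is affected, it reads as an exclusion decided by the data.

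**4. What the sample size section implies.** The stated size reproduces. The pilot means 2.48, 2.02 and 1.88 give a sum of squared deviations of 0.1971. With σ = 0.60 (the largest pilot SD), Δ = 0.1971/0.36 = 0.547. With λ = 9.635 (2 df, α 0.05, power 0.80), n = 9.635/0.547 = 17.6, so 18 per arm. Then 18 × 1.2 = 21.6, so 22 per arm and 66 in total. Enrolling 22 to keep 18 suggests that dropouts are expected not to be evaluable, which is a hint rather than a rule of analysis.

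**5. Size per patient (illustration).** If one of 22 patients in an arm with mean m has baseline b carried forward, and would otherwise have had the arm's average outcome, the arm mean changes by −(m − b)/22. The protocol gives no baseline d', so two values of b are assumed: 1.6, and 1.88 (the pilot sham mean after treatment, that is, no change under sham). The pilot gamma–sham difference is 2.48 − 1.88 = 0.60.

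- One gamma patient, b = 1.6: 0.88/22 = 0.04, so 0.60 becomes 0.56.
- One gamma patient, b = 1.88: 0.60/22 = 0.027, so 0.60 becomes 0.573.
- One sham patient, b = 1.6: the sham mean falls by 0.28/22 = 0.013, so 0.60 becomes 0.613. With b = 1.88 nothing changes.

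The direction depends on the arm in which the loss occurs. A total would need the number of such patients by arm, which the protocol does not give.

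**The case against.** The strongest reply is that the protocol is largely coherent. The dropout list, by its own words, stops interventions. The data collection section then covers exactly those patients, and the analysis section keeps them through intention to treat. That stands: for mistaken inclusion and incomplete records the fault is ambiguity, not contradiction. A reader might infer from the Dropout criteria heading that these patients are removed from the efficacy analysis. No section says so.

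It is also fair that unblinding is confined to critical emergencies and that the recorded data are kept and examined. Both limit the reach of the rule. Neither provides the missing endpoint.

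A reader might further infer that patients will be lost unequally by arm and that the resulting bias can be quantified. The documents do not support this. Sham patients are needled at the same points by the same procedure, so stuck or bent needles, haematoma and metal allergy can occur in every arm; only effects of the current could differ. Mistaken inclusion concerns eligibility, which is settled before allocation. The 20% dropout allowance cannot be charged to these rules either, since the dropout list also includes patients who withdraw of their own accord, whom no rewording would bring back. Finally, the dilution illustrated in the working arises through the carried-forward baseline, so it reflects the imputation method as well as the loss of the visit.

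**Conclusion.** The point holds in a limited form. The termination rule in Blinding conflicts with the data collection section and with the intention-to-treat analysis, and it can cost a patient the only post-baseline measurement of the primary outcome. The heading and item (c) of Dropout criteria are badly worded and leave sites unsure who returns for assessment.

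The effect is about 0.03 to 0.04 on a gamma–sham difference of 0.60 for each average gamma patient lost, under the assumed baselines of 1.88 and 1.6 and with 22 per arm. The total cannot be computed. Dependence on arm is plausible, because current is the only stated difference, but it is not shown. The correction is worth making because it is cheap and preserves outcomes after randomisation.

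**What to change.** Reconcile Blinding, Dropout criteria, Data collection and Statistical analysis so that stopping the intervention, leaving follow-up and leaving the analysis are defined separately. When the intervention is stopped remains for the clinicians.

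- In Blinding, replace termination from the trial with wording that keeps an unblinded patient in follow-up.
- State that any randomised patient who stops the intervention, is unblinded or was mistakenly included is asked to attend a post-treatment 1-back assessment about 4 weeks after starting, unless consent is withdrawn or the patient is medically unable, and is analysed in the randomised arm.
- Remove item (c) as a reason for dropout and treat incomplete records as missing data.
- Rename the Dropout criteria section so that its heading matches its operative sentence.

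The cost is protocol wording and a few assessments of patients no longer on treatment. Their timing must be written in, because Study design and Randomization and allocation tie the second assessment to the last session or the end of treatment, which does not define a date for someone who stops early.
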